### CT-FFR calculation

We will employ a Deep Bidirectional Long-term Recurrent Neural Network (DBL-RNN) algorithm, independently developed by Keya Medical, which integrates a Multi-Layer Perceptron (MLP) and a Bidirectional Recurrent Neural Network (Bi-RNN). The framework will consist of two core components: CCTA image processing and deep learning–based CT-FFR calculation.

In the CCTA image processing and feature extraction stage, a Multi-Layer Perceptron (MLP) will be utilized for fully automated three-dimensional coronary artery reconstruction, including centerline extraction and lumen segmentation. Based on the reconstructed coronary geometry, a series of morphological and hemodynamics-related local feature vectors will be extracted point-by-point along the vessel centerline. These feature vectors include local vascular features (e.g., coronary cross-sectional area, coronary radius, distance to the nearest upstream coronary bifurcation), local stenotic features (e.g., stenosis length and the smallest 50% coronary radius along the stenosis), and global features (including upstream and downstream vascular characteristics and stenosis features).

The deep learning component adopts a Bidirectional Recurrent Neural Network (Bi-RNN) architecture. The sequential feature vectors generated from the previous step will be input into the Bi-RNN, which enables bidirectional information propagation and simultaneously accounts for the local upstream and downstream context of each centerline point as well as its global relationship within the entire coronary tree. Through this architecture, the network will infer continuous CT-FFR values along the entire coronary artery tree.

The DBL-RNN algorithm will be trained using data from 250 patients prospectively enrolled at Beijing Anzhen Hospital. Model weights will be initialized using a calibrated normal distribution to stabilize gradients during the early training phase. To mitigate overfitting, dropout regularization with a rate of 0.5 will be applied to the hidden layers of the network. The loss function will be defined as the squared error (SE) between the CT-FFR values generated by the model and the invasive FFR measurements. Then, the network will be iteratively optimized to minimize this discrepancy, thereby driving the predicted CT-FFR values toward the invasive reference standard. Model optimization will be performed using the Adam optimizer, with a learning rate of 0.0001 and exponential decay rates for the first- and second-moment estimates (β1 = 0.9, β2 = 0.999).

Within the training cohort, internal validation will be performed using a five-fold cross-validation approach. The dataset will be randomly divided into five approximately equal folds. In each iteration, four folds will be used for model training, and the remaining fold will be used for validation. This procedure will be repeated five times, with each fold serving as the validation set once.

Upon completion of training, the model could generate continuous CT-FFR values along the entire length of each coronary artery. All coronary vessels will be labeled according to the 18-segment classification system of the Society of Cardiovascular Computed Tomography (SCCT). During the validation phase, invasive coronary angiography images acquired at the time of invasive FFR measurement will be carefully reviewed to identify the exact anatomical location of the pressure-wire sensor within the three-dimensional coronary model. Then, the corresponding CT-FFR value at this location will be extracted, ensuring precise spatial matching between CT-FFR and invasive FFR measurements.

During the model training phase, CCTA images from the 250 patients enrolled at Beijing Anzhen Hospital will be paired with their corresponding invasive FFR measurements and used as input–output data for model training and parameter optimization.

During the model validation phase, data from 81 patients enrolled at five additional subcenters will be analyzed under a strictly blinded study design. Investigators responsible for CT-FFR computation will have access only to anonymized CCTA images and will be fully blinded to invasive FFR results, coronary angiography reports, and all clinical diagnostic information. Conversely, cardiologists interpreting invasive FFR measurements will be blinded to the CT-FFR results and will base their assessments solely on the original angiographic images and pressure recordings.

After CT-FFR values and invasive FFR measurements for the validation cohort are independently generated, a third-party investigator, who is not involved in any prior analytical steps, will match the two datasets according to predefined anonymized identification numbers. All diagnostic performance analyses will be subsequently performed by statisticians who have access only to the paired numerical values and no access to the original imaging data or clinical reports.

### Statistics

All statistical analyses will be performed using Stata version 17.0. The categorical data will be presented as counts with percentages and analyzed using the chi-squared test. Normally distributed continuous variables will be presented as the means ± standard deviations and analyzed using independent sample t-tests. Non-normally distributed continuous variables will be presented as the median (interquartile range) and analyzed using the Mann–Whitney U test. All tests will be two-tailed with p < 0.05 significant.

Baseline demographic, clinical characteristics, and angiographic characteristics, including the percentage of diameter stenosis, will be prospectively collected. These variables will be separately described in the training cohort and the external validation cohort. Comparisons between these two cohorts will be performed to assess comparability, thereby facilitating appropriate interpretation of external validation results. Because FFR primarily performed in intermediate stenosis lesions (30–90% stenosis in vessel diameter), the proportion of intermediate (30–90%) diameter stenosis lesions will be summarized and compared between the two cohorts.

Using invasive FFR as the reference standard, the diagnostic performance of CT-FFR will be evaluated at both the vessel level and the patient level. Only stented segments that undergo invasive FFR measurement will be included in the diagnostic performance analysis. Stented segments without available invasive FFR measurements will not be included in the statistical evaluation due to the absence of a reference standard.

Diagnostic performance of CT-FFR will be evaluated using invasive FFR as the reference standard. A threshold of 0.80 will be used for both CT-FFR and invasive FFR to define functionally significant lesions. Sensitivity, specificity, positive predictive value, negative predictive value, and overall accuracy will be calculated. Receiver operating characteristic (ROC) curves will be constructed, and the area under the curve (AUC) will be calculated to assess diagnostic discrimination.

At the vessel level, because a single patient may contribute more than one stented vessel, vessel-level observations may not be independent. Therefore, diagnostic performance metrics and their 95% confidence intervals will be estimated using a cluster bootstrap resampling procedure at the patient level (1000 iterations), in which patients will be sampled with replacement, and all corresponding vessel-level observations will be retained in each bootstrap sample.

Agreement between CT-FFR and invasive FFR classifications will be assessed using a cluster-adjusted McNemar test implemented with generalized estimating equations (GEE) with an exchangeable correlation structure to account for within-patient clustering. Continuous CT-FFR and invasive FFR measurements will be assessed using Spearman correlation analysis. Agreement between the two measurements will be further evaluated using Bland–Altman analysis with a linear mixed-effects model, with patient identification number included as a random effect to account for clustering. The mean bias and 95% limits of agreement will be derived from the mixed-effects model.

At the patient level, when multiple stented vessels were present, the vessel with the lowest invasive FFR value will be selected to represent that patient.

The results from the above statistical analyses will be presented in the final study report.

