**Methods:**

This study is a multicenter, prospective, diagnostic study, aiming to establish a deep learning-based CT-FFR model for the accurate assessment of ISR and to validate its diagnostic performance using invasive FFR as the reference standard. This study will be carried out in Beijing Anzhen Hospital and 6 subcenters in China.

We planned to prospectively enroll 331 post–stent implantation patients with available CCTA data since June 2022, and invasive FFR will be performed within 3 months when clinically indicated. Patient recruitment is currently ongoing. Among them, 250 patients from Beijing Anzhen Hospital will be used to adapt and extend the existing DEEPVESSEL model, a deep learning–based CT-FFR computational software designed for the non-invasive functional assessment of coronary artery disease and previously validated in de novo coronary lesions, for application in the assessment of in-stent restenosis (ISR), and 81 patients from the other 6 subcenters will be used in external validation. Sensitivity, specificity, accuracy, positive predictive value, and negative predictive value with their corresponding 95% confidence intervals (CIs) were calculated for CT-FFR. The receiver operating characteristic (ROC) curve was analyzed, and the area under the curve (AUC) was calculated. The McNemar test and Bland-Altman plot will be used to examine the diagnostic consistency between CT-FFR and invasive FFR. The correlation was analyzed by Spearman’s correlation coefficient.

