### Sample size calculation

The sample size calculation was based on previous studies [19] and the following hypothesis: At the patient level, CT-FFR demonstrated an AUC of 0.73(95% CI: 0.55–0.87) for detecting ISR, with a disease prevalence of 76%. A sample size calculation was performed using PASS 2021 (Test for One ROC Curve) with α = 0.05, power = 0.9, and two-tailed testing, yielding a required sample size of 77 patients. We planned to prospectively enroll 81 patients in the external validation cohort, which was expected to provide 90% power to detect an AUC of 0.73.

The training cohort size was defined based on data availability and a predefined training-to-validation ratio of approximately 3:1 to balance model development and independent performance evaluation. Therefore, at least 243 patients were required for model training. Considering clinical practice and data availability, we prospectively planned to enroll 250 patients to meet the sample size requirement, which is comparable to or even larger than the training cohort sizes reported in previous study [20].

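### The McNemar test named as the assessment of agreement tests only whether CT-FFR and invasive FFR have equal positive rates, not how often they agree

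*Protocol article*

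**What the plan says.** Both methods are dichotomised at the same cut-off: "A threshold of 0.80 will be used for both CT-FFR and invasive FFR to define functionally significant lesions" (Statistics). For the resulting yes/no classifications the section continues: "Agreement between CT-FFR and invasive FFR classifications will be assessed using a cluster-adjusted McNemar test". The test is to be fitted by generalized estimating equations with an exchangeable correlation within patient. The abstract (Methods) assigns the same role: "The McNemar test and Bland-Altman plot will be used to examine the diagnostic consistency between CT-FFR and invasive FFR". The only rule for reading a p-value is the general one, "All tests will be two-tailed with p < 0.05 significant".

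The Statistics section also plans sensitivity, specificity, predictive values, overall accuracy and AUC. At vessel level the performance metrics get 95% intervals from a bootstrap that resamples patients. Agreement of the continuous values is covered by a Bland-Altman analysis with a patient random effect. For correlation the text says only: "Continuous CT-FFR and invasive FFR measurements will be assessed using Spearman correlation analysis". No kappa or other chance-corrected index is named. The Discussion expects a strong correlation and good diagnostic consistency.

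**The concern.** Agreement asks how often two classifications coincide. McNemar asks whether the two methods have the same positive rate. The questions differ: a method can match the reference's positive rate while misclassifying many individual vessels, and it can agree in nearly all vessels while its few errors all point one way. A p-value from this test therefore cannot support or refute agreement in either direction. In addition, failing to reject equality is not evidence of equality.

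At stake is the statement on categorical agreement or diagnostic consistency in the final report. This is a matter of what the protocol states, not of detail left to an analysis plan: the method named does not answer the question it is given.

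**Working it through.** **Plan's own figure.** The article gives no figure for the McNemar test. Its one sample-size figure, 77 patients for the AUC test, is reproduced closely: AUC 0.73 against an assumed null of 0.50 (the null is not stated), prevalence 76%, two-sided alpha 0.05 and power 0.90 give 78 patients with the Hanley-McNeil variance. That figure is not in dispute.

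**Inputs.** From Sample size calculation: "We planned to prospectively enroll 81 patients in the external validation cohort", "with a disease prevalence of 76"%. So 0.76 × 81 ≈ 62 FFR-positive and 19 FFR-negative. Assumption: one vessel per patient. The 76% is a patient-level figure, and the article gives neither a vessel-level prevalence nor the number of vessels per patient.

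**What is tested.** Let b = false negatives and c = false positives.

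- CT-FFR positive rate minus FFR positive rate = (TP + FP)/N − (TP + FN)/N = (c − b)/N. The concordant cells cancel.
- Exact McNemar: p = min[1, 2 × P(Bin(b + c, 0.5) ≤ min(b, c))].
- In its usual GEE form, the model regresses the classification on method (CT-FFR or FFR) and tests the method coefficient against zero. The clustering adjustment does not change that null hypothesis of equal positive rates.
- Kappa = (po − pe)/(1 − pe), with po = (TP + TN)/N and pe the agreement expected by chance from the margins.

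**Table A: TP/FN/FP/TN = 47/15/15/4.**

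- McNemar: b = c = 15, so p = 1.00.
- Accuracy po = 51/81 = 63.0%; sensitivity 47/62 = 75.8%; specificity 4/19 = 21.1%.
- pe = (62 × 62 + 19 × 19)/81² = 4205/6561 = 0.641.
- Kappa = (0.630 − 0.641)/(1 − 0.641) = −0.03.

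**Table B: 54/8/0/19.**

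- McNemar: p = 2 × 0.5⁸ = 0.008.
- Accuracy po = 73/81 = 90.1%; sensitivity 54/62 = 87.1%; specificity 100%.
- pe = (62 × 54 + 19 × 27)/81² = 3861/6561 = 0.588.
- Kappa = (0.901 − 0.588)/(1 − 0.588) = 0.76.
- Positive rates: 54/81 = 66.7% by CT-FFR and 62/81 = 76.5% by FFR.

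**Difference in positive rates with its interval.** SE = √[(b + c) − (b − c)²/N]/N.

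- Table A: difference 0; SE = √30/81 = 0.068; 95% CI −13.3 to +13.3 percentage points. Even on McNemar's own question, p = 1.00 leaves a wide range open.
- Table B: difference −8/81 = −9.9 points; SE = √(8 − 64/81)/81 = 0.033; 95% CI −16.4 to −3.4 points.

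**How often this occurs.** 20,000 simulated trials per row, N = 81, prevalence 0.76, one vessel per patient:

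| Sensitivity / specificity | Expected accuracy | McNemar p < 0.05 (exact) | McNemar p < 0.05 (chi-square) |
|---|---|---|---|
| 0.76 / 0.24 (unrelated to FFR) | 63.5% | 3.0% | 5.4% |
| 0.90 / 0.90 | 90.0% | 18.8% | 29.2% |
| 0.90 / 1.00 | 92.4% | 58.8% | 87.3% |

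The first row is non-significant in about 95 to 97% of trials although the classification is unrelated to FFR. In the second row, expected false negatives are 81 × 0.76 × 0.10 = 6.2 and expected false positives 81 × 0.24 × 0.10 = 1.9. At high prevalence, equal error rates still produce unequal positive rates.

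**The case against.** **A useless model could not pass unnoticed.** This is right. Table A would be reported with specificity 21% and accuracy 63%, and the sample size rests on the AUC, not on McNemar. A reader might infer that the plan would let a worthless model be declared adequate; the planned accuracy measures contradict that. Overall accuracy against FFR is also arithmetically the same as percent agreement, so one proper agreement measure is already planned, with a vessel-level bootstrap interval.

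**The article does not say that a non-significant p-value will be read as consistency.** This also stands. The Discussion names an expected outcome but ties it to no test, and the abstract lists McNemar beside Bland-Altman. A reader might infer such a decision rule, but none is written. The words that assign agreement to McNemar are written, and they are the point here. Bland-Altman concerns the continuous values, not the classification at 0.80.

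**In Table B the test is doing its job.** Agreed. Eight false negatives and no false positives is one-sided under-calling, which matters for a diagnostic test. The example does not show McNemar to be wrong; it shows that a significant result is no sign of poor agreement.

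**The numbers mix levels.** Also fair. A patient-level prevalence is applied to a vessel-level test. The tables show what can happen, not what will. The null hypothesis of the test does not depend on that assumption.

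**Spearman.** The article gives a clustering method to the other vessel-level analyses and none to Spearman. A reader might infer that its interval and p-value would treat vessels of one patient as independent. The article describes neither for Spearman, so that is not established.

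**Conclusion.** The point holds in a limited form. The protocol article names a test of equal positive rates as the assessment of agreement, in the abstract and again in Statistics. That test cannot show how often the classifications agree: under the stated assumptions, p = 1.00 can go with kappa −0.03, and p = 0.008 with accuracy 90% and kappa 0.76. That it tests only equal positive rates is a property of the method and needs no assumption. The sizes rest on 81 patients, 76% prevalence and one vessel per patient.

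The damage is confined to the conclusion on categorical agreement. The accuracy estimates, the AUC and the sample size are unaffected. It should be corrected, but it does not threaten the study as a whole.

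**What to change.** 1. Base the conclusion on categorical agreement on the overall accuracy already planned, named also as percent agreement, together with Cohen's kappa. Take both 95% intervals from the patient-level cluster bootstrap already planned. Kappa is needed beside accuracy because at 76% prevalence a classification unrelated to FFR with the same positive rate already agrees in 0.76² + 0.24² = 63.5% of cases. Other chance-corrected indices exist; the choice should be fixed in advance.
2. Relabel the McNemar/GEE analysis, in Statistics and in the abstract, as a check for systematic over- or under-calling. Report the difference in positive rates (CT-FFR minus FFR) with its 95% CI.
3. State that a non-significant result of that test is not evidence of agreement.
4. As a minor addition, take any vessel-level interval for the Spearman coefficient from the same cluster bootstrap.

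The cost is a few sentences of wording and a few lines of code. No further patients or data are needed, and the article reports recruitment as ongoing, so the change can be made before the analysis.

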## Discussion

This study is a multicenter, prospective, diagnostic study, aiming to establish a deep learning-based CT-FFR model for the accurate assessment of ISR and to validate its diagnostic performance using invasive FFR as the reference standard. The expected outcome is a strong correlation and good diagnostic consistency between the CT-FFR model and invasive FFR. Through the development of this model, the anatomical and functional assessments of ISR lesions are effectively integrated, reducing the impact of stent structure and other factors on CCTA image quality. This model enables precise diagnostic results without invasive procedures, significantly optimizing the diagnostic process and improving treatment efficiency.

Previous studies on CT-FFR have primarily focused on de novo coronary lesions, with limited research on the CT-FFR model for ISR lesions. Therefore, this study specifically constructs a CT-FFR model for ISR lesions. Compared to other studies, this study was based on a fully automated CCTA image processing and deep learning–based analytical framework using a Deep Bidirectional Long-term Recurrent Neural Network (DBL-RNN) for CT-FFR estimation. The framework performs automated three-dimensional reconstruction of the coronary arteries and centerline-level feature extraction. Local vascular morphology, stenosis-related characteristics, and upstream and downstream global information are integrated within a bidirectional recurrent neural network, which captures relationships along the vessel path and the overall structure of the coronary artery tree. As a result, continuous CT-FFR values can be estimated along the entire coronary artery. During model training, dropout regularization and Adam optimizer were applied to improve model stability and generalizability, providing a novel approach for non-invasive functional assessment of coronary lesions.

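### Minor: the Spearman correlation of CT-FFR with invasive FFR has no clustering adjustment and no stated level, unlike the analyses beside it

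*Protocol article*

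**What the plan says.** The vessel-level part of the Statistics section opens with its reason for adjusting: "because a single patient may contribute more than one stented vessel, vessel-level observations may not be independent". Three methods follow from it.

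- Diagnostic performance metrics and their intervals "will be estimated using a cluster bootstrap resampling procedure at the patient level (1000 iterations").
- Classification agreement uses a "cluster-adjusted McNemar test implemented with generalized estimating equations (GEE) with an exchangeable correlation structure to account for within-patient clustering".
- The Bland-Altman analysis uses a linear mixed model, "with patient identification number included as a random effect to account for clustering".

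Between the second and third stands the sentence on correlation: "Continuous CT-FFR and invasive FFR measurements will be assessed using Spearman correlation analysis". It names neither a level of analysis nor a way to handle several vessels per patient. The Abstract also names Spearman's coefficient without adjustment. The patient-level rule comes afterwards in its own paragraph: "the vessel with the lowest invasive FFR value will be selected to represent that patient".

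The Discussion then forecasts: "The expected outcome is a strong correlation and good diagnostic consistency between the CT-FFR model and invasive FFR".

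**The concern.** The plan gives a reason to doubt independence between vessels and acts on it for the analyses on either side of the correlation, but not for the correlation. A statistician following the text would run the standard Spearman procedure on all vessel pairs. Its test and the usual Fisher-type interval take the number of vessels as the number of independent observations. If vessels within a patient resemble each other on both measurements, that overstates the information, so the interval is too narrow and the p-value too small.

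At stake is comparability within one results table. Rho would carry error bars computed on a different footing from the sensitivity, specificity and limits of agreement printed beside it, and the Discussion names correlation as one of two things it expects to show.

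**Working it through.** **Step 1. Set the CT-FFR versus FFR analyses side by side (Statistics section).**

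| Analysis | Clustering method named |
|---|---|
| Diagnostic performance metrics | Patient-level bootstrap, 1000 iterations |
| McNemar test | GEE, exchangeable correlation |
| Spearman correlation | None |
| Bland-Altman | Mixed model, patient random effect |

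The measures introduced under diagnostic performance are sensitivity, specificity, predictive values, accuracy and AUC. Correlation is not among them, so the bootstrap sentence does not plainly reach it.

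**Step 2. Inputs.** From the article: 81 patients in the external validation cohort, and two-sided testing at 0.05. Not in the article, and therefore assumed: the share *p* of patients with two vessels, the within-patient correlation (ICC, taken as equal for both measurements), and the true correlation. The article gives no figure for the Spearman analysis, so there is none to reproduce; its sample size rests on a patient-level AUC and does not bear on this point.

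**Step 3. Approximate inflation.** The naive standard error of Fisher's z for Spearman's r over *n* vessels is sqrt((1 + r²/2)/(n − 3)). With zero true correlation, clustering multiplies the variance by about

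D = 1 + (mean m² / mean m − 1) × ICC²,

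where m is vessels per patient. If a share *p* have two vessels and the rest one, mean m = 1 + p and mean m² = 1 + 3p.

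- p = 0.2, ICC 0.3: 1 + (1.6/1.2 − 1) × 0.09 = 1.03; square root 1.01.
- p = 0.4, ICC 0.5: 1 + (2.2/1.4 − 1) × 0.25 = 1.14; square root 1.07.
- p = 0.6, ICC 0.7: 1 + (2.8/1.6 − 1) × 0.49 = 1.37; square root 1.17.

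**Step 4. Simulation of the standard error and interval.** Bivariate normal vessel pairs with shared patient effects were simulated for 81 patients, with p 0.2-0.6, ICC 0.3-0.7, true correlation 0-0.7 and 2500 runs per setting. The true standard error was 0.97 to 1.14 times the naive one, and the nominal 95% interval covered 91-96%. The error is negligible with few two-vessel patients and about 8-14% with strong within-patient correlation and p of 0.4-0.6. The top value is a little below the 1.17 of Step 3, which is an approximation.

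**Step 5. Second simulation, extended to extremes.** 81 patients; 4000 runs at zero correlation, 2000 at an underlying correlation of 0.7.

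| Vessels per patient | ICC | Type I error, nominal 5% | Coverage at 0.7 |
|---|---|---|---|
| all one | any | 5% | 95-96% |
| 20% with two | 0.3 | 5.9% | 95.2% |
| 20% with two | 0.5 | 5.9% | 94.8% |
| 40% with two | 0.3 | 5.7% | 96.5% |
| 40% with two | 0.5 | 7.5% | 94.3% |
| 40% with two | 0.8 | 9.7% | 91.6% |
| all two | 0.8 | 12.4% | 88.9% |
| all three | 0.8 | 19.4% | 83.9% |

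Monte Carlo error is about sqrt(0.05 × 0.95/4000) = 0.3 points for the type I error and sqrt(0.05 × 0.95/2000) = 0.5 points for coverage.

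**Step 6. Size on the scale of rho.** With 40% giving two vessels (81 × 1.4 = 113 vessels) and correlation 0.7, the actual standard deviation of rho was 0.055 at ICC 0.3 and 0.065 at ICC 0.8. The corresponding half-widths are 1.96 × 0.055 = 0.11 and 1.96 × 0.065 = 0.13, a difference of about 0.02. At correlation 0.7 the test against zero rejected in every run of every setting.

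**The case against.** The strongest reply is that the alleged error is inferred. The article promises no interval and no p-value for rho; it has only a general rule that tests are two-sided at 0.05. If rho is reported descriptively, nothing is misstated. The level is also unstated: the plan analyses patients as well as vessels, and at patient level one vessel represents each patient, so clustering disappears. And a journal article may leave such detail to an analysis plan not shown here.

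Much of this stands and limits the point to minor. It does not remove it. The article did not defer clustering elsewhere; it named a method in the sentences around this one. The next sentence carries the same measurements into a model with a patient random effect, which needs several vessels per patient, and the patient-level rule comes only later. Vessel level is the natural reading, and if it is wrong the sentence still needs to say so.

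Some stronger readings are tempting but unsupported.

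- A reader might infer that the plan declares vessels dependent. It says only that they may not be independent.
- A reader might infer that correlation is a criterion by which the model is judged. The Discussion sentence is a forecast, with no threshold or decision rule; the stated objective is diagnostic performance.
- A reader might infer that every other vessel- or lesion-level result is adjusted. The between-cohort comparison of the proportion of lesions with 30-90% stenosis also names no clustering method.
- A reader might take the 19% type I error as the likely size. It needs all 81 patients to contribute three vessels at ICC 0.8, while only stented segments with an invasive FFR measurement count.

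**Conclusion.** The point holds as a minor inconsistency: by its position the Spearman analysis is at vessel level, and it is the one CT-FFR versus FFR comparison there without a clustering method. Followed literally, an ordinary p-value or interval for rho would rest on independence between vessels.

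Over the moderate range in Step 4 the understatement of the standard error runs from nil to about 14%. It vanishes with one vessel per patient and grows beyond that range only with many vessels per patient and high within-patient correlation. All of this depends on assumed vessel counts and ICCs, on an interval or test being reported, and on normally distributed patient effects. The consequence is for the quoted precision of rho, not for whether a strong correlation differs from zero, and no sample size or formal success criterion depends on it.

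**What to change.** Replace the Spearman sentence in the Statistics section with wording such as: *At the vessel level, Spearman's rho between CT-FFR and invasive FFR will be reported with a 95% confidence interval obtained from the same 1000 patient-level cluster-bootstrap samples; no p-value from the independence formula will be given.* If a patient-level rho is also intended, say so; with one vessel per patient it needs no adjustment.

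The cost is one sentence and one more statistic computed on samples already being drawn. The only downside is a possibly slightly wider interval. The article reports recruitment as ongoing, with analysis to be finalised in 2026, so the change can still be fixed before the results are known.

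### The Bland-Altman analysis reports one mean bias and one pair of limits, although training on squared error makes a difference that varies with FFR level likely

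*Protocol article*

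**What the plan says.** The Statistics section of the protocol article describes the agreement analysis of the continuous values as a Bland-Altman analysis in a linear mixed-effects model, "with patient identification number included as a random effect to account for clustering". The output is then fixed: "The mean bias and 95% limits of agreement will be derived from the mixed-effects model". The same section adds a rank correlation: "Continuous CT-FFR and invasive FFR measurements will be assessed using Spearman correlation analysis". The abstract also announces a graph: "The McNemar test and Bland-Altman plot will be used to examine the diagnostic consistency between CT-FFR and invasive FFR".

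The section on CT-FFR calculation states how the model is fitted: "The loss function will be defined as the squared error (SE) between the CT-FFR values generated by the model and the invasive FFR measurements". It continues that "the network will be iteratively optimized to minimize this discrepancy".

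For classification, the Statistics section says: "A threshold of 0.80 will be used for both CT-FFR and invasive FFR to define functionally significant lesions". Sensitivity, specificity, predictive values, accuracy and AUC are planned alongside. The Discussion gives strong correlation and good diagnostic consistency as the expected result.

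**The concern.** One bias with one pair of limits describes agreement properly only when the difference (CT-FFR minus invasive FFR) has the same mean and spread over the whole FFR range. The plan's own loss function works against this. A predictor that minimises squared error shrinks toward the mean to the extent that it cannot explain the outcome, so its values are less spread than the measurements. The differences then tend to be positive where FFR is low and negative where it is high, and they cancel in the mean.

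The other planned summary of the continuous values would not reveal this, because Spearman correlation uses ranks and is unaffected by compression of the scale. A report could therefore show a good rank correlation and a mean bias near zero, in line with the expected conclusion, while low values are read systematically high. The single pair of limits would be off-centre at both ends of the range.

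**Working it through.** **The plan's own figure.** The protocol gives no numerical target for agreement. Its one computed figure is the AUC sample size, "with α = 0.05, power = 0.9, and two-tailed testing, yielding a required sample size of 77 patients". With AUC 0.73, prevalence 76% and an assumed null AUC of 0.50 (the null is not stated), the Hanley-McNeil variance gives 78 patients. That agrees closely with 77. The present point does not depend on it.

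**Inputs.** From the protocol: squared-error loss, prevalence 76% at FFR ≤ 0.80, and 81 validation patients. Assumed, because the protocol gives neither: correlation r between CT-FFR and FFR from 0.5 to 0.9, and FFR normally distributed with SD s = 0.10. The slopes do not depend on s. These inputs place the cohort mean at 0.80 - 0.10 × 0.706 = 0.729.

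**Slope.** Let P be CT-FFR, F invasive FFR, D = P - F and A = (P + F)/2. For a calibrated squared-error predictor, Var(P) = Cov(P,F) = r²s², and the mean of D is 0. Then:

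- Cov(D,A) = (Var P - Var F)/2 = -s²(1 - r²)/2
- Var(A) = s²(1 + 3r²)/4
- slope of D on A = -2(1 - r²)/(1 + 3r²)

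Example at r = 0.7: -2 × 0.51/2.47 = -0.41.

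**Size.** The constant limits are 0 ± 1.96 s√(1 - r²). The bias within a band of averages comes from simulation.

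| r | slope on average | constant limits | bias, averages 0.60-0.65 | bias, averages 0.85-0.90 |
|---|---|---|---|---|
| 0.5 | -0.86 | ±0.170 | +0.086 | -0.12 |
| 0.7 | -0.41 | ±0.140 | +0.04 | -0.06 |
| 0.9 | -0.11 | ±0.085 | +0.011 | -0.016 |

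The overall mean bias is 0.00 in every row.

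**Coverage of the constant limits.** At averages of 0.55-0.60 and 0.85-0.90, nominal 95% limits contain about 74-78% of differences when r = 0.5 and 89-90% when r = 0.7.

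**Where the sign changes.** The expected difference is zero at the cohort mean, 0.729 here. Just below and just above the cut-off it is negative on both sides. For averages of 0.75-0.80 and 0.80-0.85 it is -0.037 and -0.078 at r = 0.5, and -0.018 and -0.038 at r = 0.7.

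**Which r is plausible.** The protocol does not say. Under bivariate normality with the cut at 0.80, the planning AUC of 0.73 corresponds to r of about 0.45 to 0.50. That AUC comes from an earlier study, so it only indicates that the steeper rows cannot be dismissed.

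**The slope is not certain.** At r = 0.7 the slope on the average is 0 if Var(P) = Var(F), and +0.24 if Var(P) = 1.5 Var(F), as overfitting or a shift between hospitals could produce.

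**Can 81 patients estimate it?** In 200 simulated trials per value of r (81 patients, 20% with two vessels, within-patient correlation 0.3, cohort mean set at 0.76), a regression of D on A detected the slope in about 100% of runs for r ≤ 0.7, 97% at r = 0.8 and 63% at r = 0.9.

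**The case against.** The case on the other side has five parts.

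- **The slope does not follow from the loss alone.** Squared error fixes an optimum in the training data. Here an existing model is adapted on 250 patients and tested at other hospitals, where the spread of predictions may differ. This stands: the slope is expected, not guaranteed.
- **A reader might infer that the errors have opposite signs on either side of 0.80.** The calculation does not support that. The sign changes near the cohort mean, and close to the cut-off both sides share a sign.
- **A reader might infer that a negative slope shows CT-FFR readings to be miscalibrated.** It does not. A calibrated predictor has zero mean error at any given CT-FFR reading, including 0.80, and still shows this slope on the average because the two variances are unequal. The fix must be worded accordingly.
- **The pattern would not be wholly hidden.** The Bland-Altman plot would display a steep trend, and sensitivity and specificity at 0.80 would register misclassification. At r = 0.5, for example, they are about 0.96 and 0.20. This stands in part: neither yields a slope, an interval or corrected limits.
- **The section does not say that the bias is constant and does not exclude further fixed effects,** which an unseen analysis plan could add. This also stands, so there is no error or contradiction here. The article does, however, name the model, its random effect and the quantities to be reported, and that stated output can be improved.

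The largest biases also concern few patients: at r = 0.5 the 0.85-0.90 band of averages holds about 2 of 81.

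**Conclusion.** The point holds as an inexpensive improvement to a stated supporting analysis. It is not an error in the plan, and it does not touch the AUC on which the sample size rests. A single mean bias and one pair of limits are adequate only if the difference is unrelated to FFR level, and squared-error training makes that unlikely unless the correlation is high. The effect ranges from large (slope -0.86 at r = 0.5) to small (-0.11 at r = 0.9). It rests on an assumed r, on calibration and, for the biases in FFR units, on an assumed normal FFR distribution with SD 0.10. The recommendation does not depend on the direction, because a constant-bias summary is equally inadequate if the slope proves positive at the external hospitals.

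**What to change.** In the planned mixed model, add the pairwise average of CT-FFR and invasive FFR, centred at its cohort mean, as a fixed effect. Report its slope with a 95% CI. Beside the overall mean bias, give the bias and limits of agreement at several values of the average, including 0.80. State in advance that a negative slope will be described as compression of range (unequal variances) and not, by itself, as miscalibration of a given CT-FFR reading.

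The cost is one extra model term and a less simple agreement summary. No new data are needed, and the protocol reports that enrolment is still under way, so the change can still be prespecified.
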